#### Intervention implementation

Based on the CBO’s existing HIV and STD prevention methods, such as HIV and STDs testing services, we construct a new integrated intervention model for HIV and STDs control among MSM by adding two parts of interventions.

The first part is to strength MSM’s safety awareness of seeking sexual partners and sense of health self-responsibility. Two measures will be implemented as follows: (1) Provide health education materials weekly to participants through the WeChat official account and app’s health education module. These materials contain the harmfulness of HIV/AIDS and STDs, symptoms and signs of HIV/AIDS and STDs, awareness of receiving HIV and STDs testing on their own initiative, awareness of partner notification, HIV/AIDS and STDs prevention skills, related laws, related drug use instruction, and the harmfulness of drug abuse and its prevention. The content of health education will repeat every 6 months in order to ensure all participants receive the whole education content. (2) Provide HIV and STDs testing prompting service to HIV negative participants monthly according their test records individually through app’s prompt and warning module and mobile phone short messages.

The second part is to promote and encourage partner notification through the app. We expect if two MSM are dating through some online dating platforms, the partner notification and related warnings provided via the app will in a timely manner help them know each other’s HIV and STDs status before they are going to meet and have sex.

This research is designed as a pragmatic SW-CRCT study. The interventions participants received in the control period and the intervention period are different. In control period, they will receive health education through the WeChat official account and app, as well as HIV and STDs testing prompting service. The app’s test result self-query module is also opened to them to promote the use of the app and avoid the loss to follow-up. But the partner notification is not available. In intervention period, all interventions in the control period will continue, and the partner notification functions will be opened. (Fig. 1).

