### Sample size

We used the *steppedwedge* procedure in Stata software set for SW-CRCT design to calculate the sample size. We assumed the HIV incidence was 7% in the control status, and could be reduced to 5% after partner notification intervention. The parameters set for sample size calculation include: (1) The number of clusters was 16; (2) The number of steps was 4, with 4 clusters in one step; (3) α was set as 0.05; (4) Power was set as 0.90; (5) ICC (ρ) was set as 0.01. The total sample was 4320 (270 for each clusters). Considering most studies of MSM showed a high proportion of loss to follow up, we set a 30% loss to follow up in this research. The total sample size was 6172.

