### Outcomes

The primary outcomes of this research are the HIV positive seroconversion rate (HIV incidence) and the additional cost of the intervention. The HIV positive seroconversion rate is calculated as the number of HIV positive seroconversions divided by the total number of person-years. The additional cost of the intervention is calculated as the total cost and average cost for per participant of the integrated intervention model and each additional intervention/service based on the existing HIV prevention measures provided as before.

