The second outcomes of this research include: (1) Positive seroconversion rate (incidence) of syphilis, hepatitis B, and hepatitis C. These indicators are calculated separately as the number of syphilis/hepatitis B/hepatitis C seroconversions divided by the total number of person-years. (2) HIV and related STDs transmission among social networks. Based on the partner notification information, we will construct the transmission networks of HIV and other STDs (syphilis, hepatitis B, and hepatitis C) among participants, and analyze the characteristics of these networks and factors associated with transmission of these diseases. (3) Testing adherence. This indicator is calculated as the proportion of participants whose every adjacent testing interval is no more than 3 months as recommended by China CDC. (4) Additional cost for finding per seroconversion. This indicator is calculated through the total additional cost of the integrated intervention model based on the existing HIV prevention measures provided as before divided by the total number of the HIV and STDs seroconversions. (5) Frequency of utilization for each intervention/service. This indicator is calculated through the total and average frequency of utilization for each intervention/service, such as health education, partner notification, HIV and STDs testing and so on. (6) Satisfaction of the interventions and services, measured through the follow-up questionnaires by the degree of satisfaction for participants of HIV and STDs testing service, health education, partner notification and other app’s functions. (7) Knowledge of HIV and related STDs. This indicator is measured by the baseline and follow-up questionnaires. The score of knowledge questions in the questionnaires will be used to represent participants’ level of knowledge. (8) Health self-responsibility awareness, including attitudes of HIV and STDs testing, safe sexual behaviors and partner notification. The attitudes are collected by questions in the baseline and follow-up questionnaires. (9) Sexual behaviors. They are measured through questionnaires, including questions about the number of different kinds of sexual partners, frequency of anal sex, condom use, and partner notification implementation. (10) Substance use behaviors. This indicator is measured by questionnaires about participants’ usage of methamphetamine, heroin, ecstasy, and some other sex-promoting drugs. (11) Psychological status. Self-rating anxiety scale (SAS) and Self-rating depression scale (SDS) are used to measure participants’ psychological status through questionnaires. (12) Referral rate of HIV and related STDs. This indicator is calculated as the proportion of new HIV and STDs infections who have received treatment. (Additional file 2).

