### Analysis

Descriptive analysis will be used to summarize the socio-demographic characteristics, HIV and STDs incidences, as well as knowledge, attitudes and related behaviors of total participants and different subgroups. To investigate the effects of the additional partner notification intervention, we will compare the differences of these primary and secondary outcomes in the control period and in the intervention period. As the HIV and STDs infection and most of the secondary outcomes are categorical variables, the generalized linear mixed models (GLMM) will be used for analysis. The model will include intervention status (in intervention period or not) and time as fixed effects and clusters (the districts) and individuals as random effects. The estimated effects of partner notification will be reported as risk ratio (RR) for binary outcomes and mean difference for continuous outcomes. 95% confidential intervals (CI) and *p* values will also be reported. The total and average additional costs of the intervention will be calculated to reflect the cost-effectiveness of the additional interventions, and the differences of these indicators in the control period and intervention period will be compared. Based on the connections recorded in the partner notification records of the database, social network visualization will be conducted to reflect the real connections of the participants. Social network analysis, such as calculation of degree, density, clique, degree centrality, closeness centrality, betweenness centrality, clustering coefficient, and so on, will be used to describe the characteristics of the social networks. Several transmission models of HIV and STDs will be formed to reflect the diseases transmission among MSM.

Sub-analysis will include: comparison of the effects in different age groups, different sex roles (insertive only, receptive only, both), different usage of HIV and STDs testing services (“Mailing rapid test reagent kit” only, the facility-based only, both). A sensitivity analysis will be conducted to evaluate the cluster (the district)-level effect. We will use the outcomes of each district across the follow-ups as the dependent variable, and fit a linear mixed model with the random effect of clusters (the districts).

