If one variable is missing for < 10% of participants, we will use a complete-case approach. If one variable is missing for 10 ~ 20% of participants, multiple imputation will be used if suitable; if one variable is missing for > 20% of participants, we will investigate the mechanism of missing data, and consider to set the missing data as a category.

A two-sided *p* value of 0.05 or less was regarded as significant. Statistical analyses will be done with SPSS version 21.0, Stata version 24.0, R version 3.5.1. Social network visualization will be done with Cytoscape version 3.5.1.

The results of this research will be reported to local and national stakeholders in the form of oral presentation on professional conferences and publications on journals. We will not use professional writers in writing related articles and reports. The decisions of authorship will follow conventions of the International Committee of Medical Journal Editors. We will share our study protocol, statistical analysis plan, informed consent form, study report and analytic code after completing the analysis of the whole study. If other researchers want to apply for the above information and data of this research, they should contact principal investigator. Personal information (name, unit, title, etc.), detailed description of required data (required variables, etc.), and research proposal are needed for further discussion and decision.

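### Costs alone are said to reflect cost-effectiveness; no planned indicator joins incremental cost to HIV infections averted, and the cost indicators as defined cannot compare the two conditions on value

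*Protocol article*

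**What the plan says.** The objectives at the end of the Background include an analysis of incremental cost over existing prevention measures, in order to judge cost-effectiveness. The Discussion expects a favourable answer.

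- **Co-primary cost (Outcomes).** This is the total cost and the "average cost for per participant of the integrated intervention model and each additional intervention/service based on the existing HIV prevention measures provided as before". It covers both the whole package and its separate components.
- **Secondary outcome (4) (Outcomes).** It is labelled as the cost of finding a seroconversion. It is the total additional cost of the integrated model over the measures "provided as before divided by the total number of the HIV and STDs seroconversions".
- **Control condition (Intervention implementation).** "In control period, they will receive health education through the WeChat official account and app, as well as HIV and STDs testing prompting service". Self-query of test results is open too. The intervention condition adds only the partner notification functions.
- **Use of the costs (Analysis).** "The total and average additional costs of the intervention will be calculated to reflect the cost-effectiveness of the additional interventions". The same sentence says that these indicators will be compared between the control and intervention periods. The section also plans to compare primary and secondary outcomes between the two.

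**The concern.** Three features of the cost plan stand between the data and the economic objective.

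1. Cost is treated as if it showed cost-effectiveness by itself. No indicator in the article divides an incremental cost by infections averted.
2. The package cost and outcome (4) look back to services before the app. The effect model estimates partner notification on top of education, prompts and self-query. A reader who puts the headline cost next to the headline effect would combine two different comparators.
3. Outcome (4) has in its denominator the events that the intervention is meant to prevent, and raw totals depend on how long each condition is observed. Read as between-condition results, both can point the wrong way.

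At stake is the second objective and the interpretation of a co-primary outcome. The HIV incidence analysis is not affected.

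**Working it through.** The document states no cost or cost-effectiveness figure, so there is none to reproduce. The total of 6172 used in step 4 does reproduce: 4320 / 0.70 = 6171.4, rounded up.

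**1. Which contrast each quantity measures**

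| Quantity | Reference | What is added |
|---|---|---|
| Integrated-model cost; outcome (4) numerator | Services before the app | Education, prompts and partner notification |
| Per-service cost | Services before the app | Each component separately, partner notification included |
| Modelled effect | App control (education, prompts, self-query) | Partner notification only |
| Cost difference between periods, per person-year | App control | Partner notification only |

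The last two rows match. The first row does not match the effect, and the trial has no condition without education and prompts that could supply a matching effect.

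**2. Size of the mismatch if package cost were used**

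The Sample size section gives the planned effect: "We assumed the HIV incidence was 7% in the control status, and could be reduced to 5% after partner notification intervention". It states no time unit; I read the figures as per 100 person-years, the scale of the primary outcome. Let the package cost c per person-year, with partner notification a share s of it. The documents do not give s, so a range is shown.

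- Package cost per infection averted: c / 0.02 = 50c.
- Partner notification cost per infection averted: s × c / 0.02 = 50cs.
- Overstatement: 50c / 50cs = 1/s, which is 10 at s = 0.10, 4 at 0.25, 2 at 0.50 and 1.33 at 0.75.

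**3. Direction of outcome (4)**

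For HIV alone, at equal spend c per person-year:

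- Control: c / 0.07 = 14.3c.
- Intervention: c / 0.05 = 20.0c.
- Ratio: 7/5 = 1.40.

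The protocol's denominator also counts syphilis, hepatitis B and hepatitis C, and no rates are given for these. If HIV is a share h of control-condition seroconversions and STD counts do not change, the ratio is 1 / (1 − 2h/7):

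- h = 0.50: 1 / 0.857 = 1.17.
- h = 0.25: 1 / 0.929 = 1.08.

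If STDs fall in the same proportion as HIV, the ratio returns to 1.40. Any added cost of partner notification raises it further. A sufficient rise in STD cases found could lower it, which again would say nothing about value.

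**4. Person-time behind the totals**

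Inputs: five half-year periods, with one of four groups crossing over at each step (Study design and timeline); no recruitment in the last 6 months (Study setting and recruitment); 6172 men. Assumptions: recruitment uniform over the first 2 years, equal groups, no loss.

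- Mean person-years per recruited man in periods 1 to 5: 0.0625, 0.1875, 0.3125, 0.4375, 0.5. Sum 1.5.
- Share of groups in control: 1, 0.75, 0.5, 0.25, 0.
- Control share of person-time: (0.0625 × 1 + 0.1875 × 0.75 + 0.3125 × 0.5 + 0.4375 × 0.25) / 1.5 = 0.46875 / 1.5 = 0.3125.
- Total: 6172 × 1.5 = 9258 person-years; control 2893, intervention 6365; ratio 2.2.

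At identical spend per person-year, total cost in the intervention condition would therefore be about 2.2 times that in control, from exposure alone.

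**The case against.** The strongest reply is that the plan already holds what is needed. The co-primary outcome also costs each added service, partner notification among them, and the Analysis section compares cost indicators between control and intervention periods. On a common person-time base that difference is the partner notification increment, the same contrast as the modelled effect. The article nowhere divides package cost by the effect of partner notification, and costing the package against prior services is a legitimate budget question. This stands. A reader might infer that cost-effectiveness cannot be concluded from this trial at all; the documents do not support that.

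Second, outcome (4) is labelled a case-finding cost, and the sentence on cost-effectiveness refers to total and average costs, not to this ratio. That also stands: the protocol does not say that the ratio will rank value. But it is the only cost ratio in the plan, and secondary outcomes are to be compared between conditions, so the misreading is easy.

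Third, 40% is not the change in outcome (4) as defined, because the denominator includes STDs, and the 2.2-fold figure depends on a recruitment pattern that the protocol does not state. Both limits are accepted.

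Fourth, perspective, time horizon, threshold and interval method may sit in an analysis plan that is not shown. They are not counted here. The point rests on what the article does state: that costs alone reflect cost-effectiveness.

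**Conclusion.** The concern holds in a limited form. As written, the cost indicators do not answer the cost-effectiveness objective: costs alone are given that role, and no indicator links incremental cost to infections averted. The planned data would allow the answer, since the matching increment can be derived.

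Package cost should not be set against the partner notification effect; doing so would overstate cost per infection averted by 1/s, where s is not in the documents. Outcome (4) and raw totals are unsuitable for comparing value between conditions. Outcome (4) rises by up to 40% when the planned effect is achieved at equal spend, if STDs fall by no more than the same proportion, and by 8% to 17% if STD counts do not change and HIV is 25% to 50% of events. Totals differ about 2.2-fold under uniform recruitment, equal groups and no loss. The direction of outcome (4) with STD counts unchanged is firmer than any of these sizes.

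**What to change.** In the Outcomes and Analysis sections:

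- State the cost-effectiveness measure as incremental cost per person-year of the intervention condition over the trial's control condition, divided by the model-based HIV rate difference (control minus intervention). The result is incremental cost per HIV infection averted.
- The Analysis section reports a risk ratio for binary outcomes, so say that the rate difference will be derived from the fitted model.
- Give an interval that respects clustering by district, for example by resampling whole districts. Report the cost increment and the rate difference separately as well, because the ratio becomes unstable when the rate difference is close to zero.
- Compare costs between conditions per person-year, not as raw totals.
- Keep the integrated-package cost (a budget figure against prior services) and the cost per seroconversion found (a case-finding yield) as description only.

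The cost is a change of wording and one small calculation from costs already planned by service. The ratio's interval may be wide. The article reports that recruitment had not begun when it was written.

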## Methods/design

### Study design and timeline

This research will use a stepped wedge cluster randomized controlled trial (SW-CRCT) design. It is commonly used to evaluate service delivery or policy interventions of clusters [26]. This research will be implemented in Beijing, whose sixteen districts are defined as the clusters. We assign the sixteen districts into four research groups using stratified randomization, with four districts in one group. The open cohort SW-CRCT will last 2.5 years, which is anticipated to be conducted from July, 2020 to December, 2022. Five continuous observational periods at a 6-month interval are divided. According to the standard design of SW-CRCT, in the first 6-month “the initial period”, no group is exposed to the additional partner notification intervention. After that, the four groups begin to cross from the control condition to receive the partner notification intervention sequentially at 6-month intervals. Once one group receives the partner notification intervention, the intervention will continue until the end of the research. And at the last 6-month period, all of the four groups will receive the additional partner notification intervention. (Fig. 1).

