### Study setting and recruitment

We will conduct our research in Beijing, the capital city of China with high population mobility and demographic heterogeneity and high burden of HIV and related STDs among MSM. We will cooperate with a local community-based organization (CBO) named *Man Wellness Center* to recruit participants and provide HIV and other STDs (syphilis, hepatitis B, and hepatitis C) testing services. *Man Wellness Center* is one of the largest and most popular CBO for MSM to give them HIV and STDs prevention and medical services.

Participants will be recruited in two ways: offline and online. The offline recruitment will be implemented in offline venues, such as the clinic sites of the CBO for routine work, and the gay bars, bathrooms, parks for outreach services. The online recruitment will be implemented through online platforms, such as WeChat, QQ, Weibo and Blued. The process of recruitment includes four steps: (1) Determine whether the participant recruited meets the eligibility criteria. (2) Introduce the research and tools for interventions (the app and the WeChat official account) if eligible. (3) Help the participant sign the electronic informed consent through the app and then show him the functions of the app and WeChat official account. The content of the electronic informed consent contains all necessary information as traditional paper version of informed consent, and the signed electronic informed consent will be stored in the database. Participants under the age of 18 are asked to register the app system and sign the consent accompanied by a guardian, and written consent is also obtained from the guardian. (4) Invite the participant to fill in the baseline questionnaire through the app. (5) Provide HIV and other STDs testing services and upload the test results through the backend database. The recruitment will start from the beginning of the research, and we will stop recruitment in the last 6 months of the research. If the participant has HIV and other STDs testing during the follow-up period, he will be invited to finish a follow-up questionnaire.

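### The co-primary cost outcome is a total and a per-participant average compared between conditions without a person-time base, so it generally differs by calendar alone; raw utilisation figures share the problem

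*Protocol article*

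**What the plan says.** All references are to the protocol article.

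- **Outcomes, primary.** HIV incidence is defined as "the number of HIV positive seroconversions divided by the total number of person-years". The co-primary cost, in the same paragraph, is "calculated as the total cost and average cost for per participant of the integrated intervention model" and of each added service. It has no time denominator.
- **Outcomes, secondary item 5.** Utilisation is "calculated through the total and average frequency of utilization for each intervention/service", again with no time denominator. Item 1 (syphilis, hepatitis B and C) does use person-years.
- **Analysis.** After describing total and average additional costs, the section states that "the differences of these indicators in the control period and intervention period will be compared". This follows the description of the generalized linear mixed model (GLMM) and is not linked to it. The GLMM has intervention status and time as fixed effects, and district and individual as random effects. The district-level sensitivity model names only a random district effect.
- **Study design and timeline.** The cohort is open, with five 6-month periods. "Once one group receives the partner notification intervention, the intervention will continue until the end of the research".
- **Study setting and recruitment.** "The recruitment will start from the beginning of the research, and we will stop recruitment in the last 6 months of the research".
- **Intervention implementation.** Health education and testing prompts belong to the added model but run in both conditions. Only partner notification is withheld under control.

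**The concern.** A total, or an average per man, grows with the time over which it is accumulated. In this design the time spent in each condition is set by when men enrol and when their district crosses. Every man enrolled by month 24 can accrue intervention time, whereas a man enrolled after his district has crossed has no control time. Education, prompts and testing recur in both conditions, so their cost and use build up with follow-up in both. A contrast of totals or per-man averages therefore mixes length of exposure with any effect of partner notification.

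The stake is one of two primary outcomes and the conclusion on affordability and cost-efficiency that rests on it. For utilisation, unchanged monthly testing could be read as increased testing.

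**Working it through.** The article gives no cost or utilisation figure to reproduce. The one stated number used is the sample size, for scale: 4320 / 0.70 = 6171.4, rounded up to 6172, as stated.

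**Inputs from the article:** 30 months; group g (1 to 4) crosses at month 6g; recruitment in months 0-24.

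**Assumptions, not in the article:** entry pattern, equal group sizes, and a constant monthly cost or use that partner notification does not change.

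**Formulas.** For entry at month t, control time = max(0, 6g - t) and intervention time = 30 - max(t, 6g).

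**Even entry over months 0-24, no loss**

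- Mean control time in group g = (6g)²/48, giving 0.75, 3, 6.75 and 12. Mean = 22.5/4 = 5.625 months.
- Mean total time = 30 - 12 = 18 months, so intervention time = 12.375 months.
- Ratio of totals = 12.375/5.625 = 2.20. For 6172 men this is about 2,893 versus 6,365 person-years.
- Share of men with any control time = mean of 6g/24 = 0.625. Control time among them = 5.625/0.625 = 9.0 months.
- Per-observed-man ratio = 12.375/9.0 = 1.375.
- Per person-month, the ratio is 1.00.

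**Even entry over months 0-6, no loss**

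- Control time = mean of (6g - 3) = (3 + 9 + 15 + 21)/4 = 12 months.
- Intervention time = mean of (30 - 6g) = (24 + 18 + 12 + 6)/4 = 15 months.
- Both ratios = 15/12 = 1.25.

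**Other patterns.** The 30% loss is the figure from the Sample size section. Its spread over 30 months is assumed.

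| Entry | Loss | Total ratio | Per-observed-man ratio |
|---|---|---|---|
| Even, 0-24 | 30% | 2.06 | 1.38 |
| Half in 0-6, rest in 6-24 | none | 1.71 | 1.28 |
| Half in 0-6, rest in 6-24 | 30% | 1.58 | 1.29 |
| Even, 0-12 | none | 1.56 | 1.36 |
| Even, 0-12 | 30% | 1.42 | 1.38 |
| Even, 0-6 | 30% | 1.11 | 1.275 |
| All at month 0 (reference only) | none | 1.00 | 1.00 |
| All at month 0 (reference only) | 30% | 0.87 | 1.03 |

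With faster loss, taken as a percentage over 18 months, entry in months 0-6 gives total ratios of 1.25, 1.03 and 0.86 at 0, 30 and 50% loss. The total ratio passes 1.00 at about 33% loss. The per-man ratio stays between 1.25 and 1.32.

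**One-off entry costs.** Let each man also incur, at entry, a one-off cost worth k months of recurring cost.

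- Even entry, no loss: 62.5% of men enter under control. Cost per observed man is 9 + k under control and 12.375 + 0.375k under intervention. These are equal when 0.625k = 3.375, so k = 5.4. The total ratio is then (12.375 + 2.025)/(5.625 + 3.375) = 14.4/9 = 1.6.
- Entry in months 0-6, no loss: everyone enters under control, so 12 + k = 15 and k = 3 brings both ratios to 1.00.
- Larger k reverses the per-man difference.

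**Period adjustment.** Under even entry without loss, months observed per active participant per 6-month period differ between conditions by 1.69 without period effects and by 0.00 with them.

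**The case against.** **The model may already deal with it.** The Analysis section says that primary and secondary outcomes are compared between the two conditions and describes a GLMM with a fixed effect of time. On participant-by-6-month rows with period effects, average utilisation would be free of the artefact, and the five 6-month periods make that a natural reading. This stands for utilisation as a possibility. The article does not state the row structure, a total cannot enter an individual-level model, and the cost comparison has its own sentence outside the model.

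**It may be detail left to the analysis plan.** A time base could be specified there. But the article does more than stay silent. It fixes a definition and a contrast for a primary outcome, beside an HIV outcome in person-years, and a plan that follows the wording reproduces the problem.

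**The direction for cost is unknown.** This stands. The article gives no cost data. One-to-one recruitment, app demonstration and baseline testing are entry costs and fall disproportionately under control, so 2.20 and 1.375 describe recurring items only.

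**Stronger readings the documents do not support.** A reader might infer that the conditions must differ unless all men enrol on day one and none is lost. The total ratios of 1.03 and 0.86 under early entry with loss, and the break-even values of k, show otherwise. A reader might also infer that the planned analysis is bound to declare a false significant difference. The article names no significance test for the cost comparison, so no error rate can be attached to it.

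**Conclusion.** The point holds for the co-primary cost as worded: the contrast is not on a common time base, and its value depends on the enrolment and crossover calendar. For recurring items with no effect, the open-recruitment patterns without loss, or with 30% loss over 30 months, give ratios of 1.11 to 2.20 for totals and 1.25 to 1.38 per man observed. Early entry with heavier loss brings the total ratio to or below 1, and one-off costs can cancel or reverse the per-man difference. It should therefore not be read as showing that partner notification will look more expensive. The uncertain sign is itself a reason not to compare these quantities.

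For utilisation the point is conditional: it applies to totals and raw averages of services offered in both conditions. It does not concern use of partner notification itself, which is unavailable under control by design. The figures rest on assumed entry and loss patterns, equal groups and a constant monthly rate.

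**What to change.** - In Outcomes (primary cost and secondary item 5), define recurring cost and utilisation per person-month of follow-up in each condition, or per participant per 6-month period.
- In Analysis, compare these with adjustment for calendar period and district, and state the row structure if the GLMM is used.
- Report one-off onboarding and baseline-test costs separately, since they arise when a man enrols and not when his district crosses.
- Show totals descriptively only, with no control-versus-intervention comparison.

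The cost is a wording change, a little more analysis work, and splitting cost records into recurring and one-off items. No extra participants are needed. Test dates and query records are among the data listed under Data management, and crossover is set by the predetermined program. Cost records and education views are not listed there, so the sponsor should confirm that they can be allocated to calendar time.
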